### 1.3. Aim

The aim of the present study is to investigate the effect of a nature-based intervention ‘The Wildman Programme’ on quality of life and symptoms of stress among men with long-term health problems compared to men receiving treatment as usual. A further aim is to investigate which natural environments in rural areas work best as supportive environments in rehabilitation. The purpose of this study protocol is to inform about the study and how it is intended to be conducted. Moreover, through the review process, the design and focus of the study can be improved.

Our expectation is that nature-based rehabilitation is suitable for men with depression and stress or long-term illnesses that can lead to depression and stress, and that the nature-based ‘Wildman Programme’ accordingly can help men with a wide variety of chronic illnesses.

Thus, we expect that the participants receiving the intervention will first and foremost experience a significant improvement in their quality of life measured by the World Health Organization Quality of Life Instruments (WHOQOL-BREF) scale [63] corresponding to a 20% improvement. WHOQOL-BREF is an abbreviated generic Quality of Life Scale developed through the World Health Organization.

Furthermore, we assume significant improvements in the other secondary effect outcomes (symptoms of stress, self-experienced restitution, and return to job) compared to the participants receiving treatment as usual (TAU). As far as we know, this type of intervention or research has never been conducted before.

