### 2.2. Participants

Inclusion criteria: The participants are men, aged 18–76 years old, living in the region of southern Funen in Denmark. The male participants are on long-term sick-leave and suffer from stress (ICD: F43.8 and F43.9), anxiety (ICD: F41.2), or depression (ICD: F32.0) according to the ICD, the International Classification of Diseases [68]. Moreover, the participants can suffer from diseases such as chronic cancer, post-cancer, chronic obstructive pulmonary disease (COPD), cardiovascular disease, or type 2 diabetes—all of which can cause stress. We expect that the nature-based ‘Wildman Programme’ can help men with a wide variety of chronic illnesses improve their quality of life and reduce symptoms of stress. Many of the participating men included in the study will in the beginning of the course to some extend experience lower quality of life and not have benefitted sufficiently from participation in other available rehabilitation interventions.

The participants will be divided into groups of 10–18 individuals in the ‘Wildman Programme’. Approximately 40% of the participants will be recruited from the health centre in the Municipality of Svendborg and the Municipality of Faaborg-Midtfyn, approximately 40% will be recruited from the jobcentre in the Municipality of Svendborg and the Municipality of Faaborg-Midtfyn, and the remaining 20% will be recruited from the general practitioners. The control group will be recruited as a form of a natural experiment from comparable departments in the health centre and the job centre and from other general practitioners.

The study will include at least 104 participants: 52 in the intervention group and 52 in the control group. The diagnoses, ages, job status, and social status of the participants will be recorded. Instead of selecting participants to be included in the intervention group and TAU by randomisation, we have chosen to follow two groups via a type of natural experiment or quasi-experiment. We choose to select the TAU group from matched health centres, job centres, and general practitioners via their normal standard routines, where the groups are matched with respect to age, gender, and diagnosis [69]. The matched control group (*N* = 52) of men will resemble the men in the intervention group with regard to the distribution of age, job status, and levels of stress to ensure that the participants in the intervention and control group are as similar as possible (see Figure 2).

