### 2.5. Outcomes

The participants all experience symptoms of stress and reduced quality of life due to their physical or mental health problems. Therefore, the following outcomes have been selected. All primary and secondary outcomes are measured at baseline (T1), post-treatment (T2), and at follow up 6 months post-intervention (T3).

Primary outcome:

The primary outcome is to investigate whether the results from the NBMC approach in the ‘Wildman Programme’ have a significant effect on the participants’ quality of life. The effect will be measured by the following scale:

Self-experienced quality of life: the World Health Organization (WHO)’s brief questionnaire, WHOQOL-BREF [80].

Secondary outcomes:

The secondary outcomes are to investigate whether the ‘Wildman Programme’ has a significant effect on the participants’ level of stress, self-experienced restitution, and job status. The effects will be measured by the following methods:Level of stress: Cohen’s Perceived Stress Scale (PSS) [81].Self-experienced restitution: The Perceived Restorativeness Scale-11 (PRS-11) [82].Job status: Measured by self-reported job status before, post, and 6 months after the intervention.

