### 3.2. Statistical Analysis

As we are dealing with a mixed group of participants, the power calculation will be based on an estimate of the medium value (*M*) and the standard deviation (*SD*). Based on population standards for men with low measures on the WHOQOL-BREF scale, the following medium value and standard deviation are estimated: *M* = 57.0, *SD* = 18.0 [63]. According to the population standards for men [83], a 20% improvement equals a change from a low global quality of life to a high global quality of life. In the light of our previous experiences with the courses and the results obtained, a medium size effect can be expected when it comes to self-reported quality of life measured with WHOQOL-BREF (Cohens d = 0.50). A t-test power calculation made by the GPower 3.1 [84] shows that there must be a total of 104 participants to obtain a medium effect on the WHOQOL-BREF (Cohens d = 0.60), by setting the significance level to 5%, the power to 80%, and the expected drop out by the 6 months’ follow up to 15%.

Data from the pilot project showed an improvement in the quality of life for the target group in relation to the mean value and standoffs.

The results of the study will be analysed according to the intention-to-treat perspective. Primary and secondary outcomes at baseline, after end of treatment, will be analysed, and again at a six months’ follow-up applying linear mixed-effects models. Missing data will be dealt with by the maximum likelihood method, as this method is regarded as the optimal method for handling missing data caused by drop out [85].

The effect of the treatment on the global quality of life mediated by the perceived restrictiveness scale is also examined by the Preacher and Hayes macro process for SPSS. The method is based on the maximum likelihood estimation and bootstrap [86].

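### Linear mixed models are fixed for every secondary outcome, including self-reported job status, which is a categorical state and not a score

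*Protocol article*

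**What the plan says.** Section 3.2 (Statistical Analysis) states: "Primary and secondary outcomes at baseline, after end of treatment, will be analysed, and again at a six months’ follow-up applying linear mixed-effects models". It makes no exception, and the article names no logistic, ordinal or other categorical model for any outcome.

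Section 2.5 (Outcomes) gives the secondary outcomes as the "participants’ level of stress, self-experienced restitution, and job status". The first two are questionnaire scales (PSS and PRS-11). The third is described only as follows: "Job status: Measured by self-reported job status before, post, and 6 months after the intervention". Section 3.1 repeats this. No categories, coding or scale are given.

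Section 1.3 (Aim) predicts significant improvements over treatment as usual in "symptoms of stress, self-experienced restitution, and return to job", so the outcome is meant to show return to work.

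Two statements in section 2.2 bear on the baseline. Eligibility: "The male participants are on long-term sick-leave". Matching: the control group is to resemble the intervention group "with regard to the distribution of age, job status, and levels of stress".

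**The concern.** A linear mixed model suits a summed score. Job status is a state that a man reports, and the article attaches no score to it. The mismatch takes a different form under each plausible coding.

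- **Several unordered categories.** The model estimates a difference in mean code. Its size and sign follow from how the categories were numbered.
- **Returned to work, yes/no.** The estimate is interpretable, but the sick-leave criterion puts nearly every man at no at T1. The variance is then close to zero at T1 and positive later, while a default linear mixed model assumes one residual variance for all visits.

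What is at stake is whether a result that the article predicts in advance can be interpreted and tested at its stated level. This is a stated rule that does not fit one of the outcomes it covers, not a detail deferred to an analysis plan: such a plan would have to depart from the text to be right.

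**Working it through.** **1. The plan's own figure.** The only sample-size figure is 104, for WHOQOL-BREF. A two-sided t-test at 5%, 80% power and d = 0.60 needs 45 per arm, 90 in total. With 15% drop-out, 90 × 1.15 = 103.5, rounded up to 104 (90 / 0.85 = 105.9, or 106). The figure reproduces and does not concern job status. It supplies the number of completers used below: 52 × 0.85 = 44.2, taken as 44 per arm.

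**2. Several categories.** Give category k the code c_k, and let Δ_k be the difference between arms in its share, with ΣΔ_k = 0. The linear model's contrast at a visit is Σ c_k Δ_k. Reversing the codes reverses the sign, and other renumberings change the size. For unordered categories no numbering is preferred, so the contrast has no fixed meaning.

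**3. Yes/no coding: variances.** Let p be the share returned to work. The variance is p(1 − p): 0 if all men are no at T1, then 0.09 at p = 0.10, 0.16 at 0.20, 0.21 at 0.30, 0.24 at 0.40 and 0.25 at 0.50. The documents give no rates, so every p is an assumption.

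**4. Yes/no coding: standard errors.** Take a random intercept, one residual variance and group-by-visit terms. This structure is assumed, because the article states none. Let v2 and v3 be the variances at T2 and T3 and c their covariance; T1 contributes nothing.

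- The residual variance estimates (v2 + v3 − c) / 3.
- Model SE of either change-from-T1 contrast: √[4 (v2 + v3 − c) / (3n)].
- True SE: √(2 v2 / n) at T2 and √(2 v3 / n) at T3.

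Example: T2 rate 10%, T3 rate 30%, n = 44, correlation 0.5 on an underlying normal scale. The joint probability of being at work at both visits is 0.0653, so c = 0.0653 − 0.03 = 0.0353.

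- Model SE = √[4 × (0.09 + 0.21 − 0.0353) / (3 × 44)] = 0.090
- True SE at T2 = √(2 × 0.09 / 44) = 0.064
- True SE at T3 = √(2 × 0.21 / 44) = 0.098

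The model SE is too large at T2 and too small at T3. Simulation of the same case gave a model SE of 0.090 against true SEs of 0.065 and 0.100, with type I error of 0.5% at T2 and 8.6% at T3.

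**5. Range.** The simulation used five pairs of T2/T3 rates (T2 0.05 to 0.30, T3 0.30 to 0.50) and correlations 0.3, 0.5 and 0.8, with equal arms:

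| T2 / T3 rate | Type I error at T2 | Type I error at T3 |
|---|---|---|
| 5% / 30% | 0.0–0.1% | 8.4–9.8% |
| 10% / 30% | 0.4–0.8% | 7.1–8.7% |
| 10% / 50% | 0.1–0.3% | 6.7–8.4% |
| 20% / 40% | 1.5–2.9% | 4.9–6.9% |
| 30% / 50% | 2.4–4.3% | 4.0–6.8% |

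The algebra explains the pattern. The T3 standard error is too small when v3 > 2(v2 − c), which happens when few men are back at work at T2 and many more at T3.

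**6. A milder setting.** With T3 rates of 10 to 40%, the T2 rate set at 0.6 of the T3 rate and correlation 0.5, the linear model rejected 5.1 to 5.9% at T3, and a plain two-proportion test 5.2 to 6.0%. There the T3 distortion is negligible.

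**The case against.** Several objections have force, and each limits what can be claimed.

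- **Baseline variation.** A reader might infer from the sick-leave criterion that job status is constant at T1. Section 2.2 does not support that in general: it expects a distribution of job status to match on, for example employed or unemployed while on leave. Near-constancy holds only for a returned-to-work coding.
- **Covariance structure.** A reader might infer that the standard errors are certainly invalid. The article specifies neither a random intercept nor a common residual variance. Robust or visit-specific variances could be defended for a binary outcome. The text does not provide for them, and if every man is no at T1 there is no T1 variance to estimate, so T1 would have to leave the response anyway.
- **Scale of the estimate.** It is tempting to say that a linear model cannot give a return-to-work probability. With 0/1 coding its contrast is a difference in probabilities. The arbitrary-code problem belongs to the multi-category coding alone.
- **Older men.** Section 2.2 admits men up to 76 ("The participants are men, aged 18–76 years old, living in the region of southern Funen in Denmark"), and a reader might infer that men past working age dilute the effect. The article gives no age distribution and no share beyond working age, and the sick-leave criterion may itself exclude most of them. An assumed 10% would turn 20 points into 20 × 0.9 = 18. Removing such men changes the question asked; it does not correct a model error.
- **Condensed article.** Item coding is commonly left to a fuller document, so its absence is not a fault. The model is stated, however, and it is stated for all secondary outcomes.

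What remains is the mismatch between the stated model and a categorical outcome, under either coding.

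**Conclusion.** The point holds in limited form. Section 3.2 fixes a linear mixed model for an outcome that is a categorical state. With several unordered categories, the result has no meaningful scale. With a yes/no coding, a default model would tend to be conservative at T2 (about 0 to 4.3% against 5%) and often liberal at T3 (4.0 to 9.8%). The size rests on assumed return rates, an assumed correlation, near-constancy at T1 and a common residual variance. In some settings T3 is close to nominal.

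The change should be made because the article predicts a significant result on this outcome. It concerns one of three secondary outcomes. The total of 104 and the WHOQOL-BREF analysis are unaffected.

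**What to change.** - Keep the linear mixed model for WHOQOL-BREF, PSS and PRS-11.
- Define the job-status categories, and derive from them a binary return-to-work outcome at T2 and T3.
- Analyse it with a likelihood-based logistic mixed model on T2 and T3. Enter baseline job status as a covariate, not as a T1 response. Report the risk difference at each visit with its 95% CI, obtained by averaging the predicted probabilities.
- If GEE is preferred, weight it or apply it after multiple imputation. Section 2.3 names return to work as a reason for drop-out, and section 3.1 collects no outcome data on men who drop out. Unweighted GEE would therefore need a stronger missing-data assumption than the maximum likelihood approach already planned. Likelihood methods ease this problem but do not remove it, since the missingness can depend on the outcome itself.
- A restriction to men in the labour market at baseline may be added as an optional sensitivity analysis, not as the main analysis.

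Cost: a change of analysis wording and a little extra programming for the risk difference, plus imputation or weighting if GEE is chosen. Job status is already collected at all three time points, and SPSS, the planned software, fits these models. Visits, recruitment and sample size stay as they are.

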## 4. Discussion

Gradually, more and more research show that the use of nature in health promotion and treatment has positive effects [24,87,88,89]. In Denmark, we still do not have the same practice to integrate nature on a strategic level in health programmes as in e.g., Sweden, Norway, and the Netherlands [90,91], but more and more development and research into nature-based interventions has taken place in Denmark in recent years [92,93].

The novelty of this study is the investigation of nature-based methods adapted to *men*, who are often an overlooked group in the healthcare system. Too many men do not seek help in the healthcare system, and they reject health offers or drop out at a much bigger scale than women. Traditionally, it has been difficult to create rehabilitation programmes that appeal to men [2]; therefore, it is important to develop and implement new methods to help men. The ‘Wildman Programme’ is designed based on the knowledge of men and their needs, and the activities are moved from inside the healthcare system to natural areas, which often appeal to many men and better resonate with their self-perception. The results of this study will be important to state whether the method in the ‘Wildman Programme’ has potential to be implemented as a rehabilitation offer in the Danish healthcare system to help men with different health problems gain better life quality and reduce symptoms of stress.

A pilot project completed prior to this study showed that nature has the potential to have a special appeal to men and that most men agree that being in nature has a positive effect on their quality of life and can increase feelings of joy, power, and peace [64,65]. In addition, the novelty of the study is to investigate whether the ‘Wildman Programme’ has a structure and contains methods that are easily accessible and easy to integrate for healthcare professionals in healthcare programmes in municipalities in Denmark. More health care professionals are asking for concrete programmes and tools they can use to support participants and patients with health problems in nature, and they are asking for recommendations on specific places in nature that are particularly favourable for nature-based interventions. This study can hopefully contribute with new knowledge on which natural environments in rural areas work best as supportive environments in rehabilitation.

### 4.1. Limitations

The intervention group and the control group will not be randomly recruited, and therefore we cannot safely determine whether they are completely comparable, even though we will match the participants regarding age, gender, and diagnosis. Instead of randomisation, we chose a method that can be described as a natural experiment or a quasi-experiment. This can be seen as a limitation, but by choosing this alternative, the risk of loss or change in the control group decreases due to dissatisfaction with not being able to belong to the intervention group, and at the same time, one can assume that the values are similar to those given in the ordinary rehabilitation. That is, this reduces threats to external validity, which often limits the value of a Randomised Controlled Trial (RCT). By using this type of design, we can involve common health centres, job centres, and general practitioners, thereby making the results more generalisable. In addition, the lack of randomisation often facilitates the recruitment of a larger proportion of eligible participants, further increasing generalisability.

### 4.2. Closure

If this study shows positive effects and significantly can improve life quality and reduce stress among men with stress, anxiety, depression, post-cancer and chronic cancer, COPD, cardiovascular disease, or diabetes type II, the ‘Wildman Programme’ has a potential to be implemented as a rehabilitation programme for men in municipalities in Denmark. Pilot projects prior to this study indicate that the NBMC approach used in the ‘Wildman Programme’ can also have beneficial effects on groups of women, groups consisting of both men and women, and on groups of young people. In a future perspective, it would be interesting to investigate the effect of the programme and the methods on new target groups.

## Figures and Tables

**Figure 1 ijerph-17-03368-f001:**
[figure not shown]
The elements in the Nature–Body–Mind–Community approach in the ‘Wildman Programme’.

**Figure 2 ijerph-17-03368-f002:**
[figure not shown]
Flowchart for the study of the ‘Wildman Programme’.

**Table 1 ijerph-17-03368-t001:** The nature qualities of the five nature environments in the ‘Wildman Programme’.

Nature Environment	Nature Qualities
Meadowland	Open landscape, rich in species, overview but still closeness to nature
Hill	Overview of the landscape, greater perspective, observation of what is happening around you
Forest	Density, darkness, wandering shade, big trees, intense sensations from sounds, scents, and sight impressions
Tunnel valley with creek	Ice Age landscape, variation in nature, trees, sound of running water is amplified
Shore	Horizon, waves and currents, sand and stones, sun and wind
